## Abstract

**Background:**

Changes in alveolar bone dimension after tooth extraction may affect placement of the subsequent implant, resulting in ridge deficiency that can adversely impact long-term implant stability or aesthetics. Alveolar ridge preservation (ARP) was effective in reducing the amount of ridge resorption following tooth extraction. There is sparse evidence regarding the benefit of ARP at periodontally compromised molar extraction sockets. This study will be a randomized trial to assess the soft tissue contour, radiographical, and histological changes of ARP at molar extraction sites in order to compare severe periodontitis cases with natural healing results and determine the most beneficial and least traumatic clinical treatment for such patients.

**Methods:**

This research is designed as a two-group parallel randomized controlled trial. The total number of tooth extraction sites will be 70 after calculation with power analysis. Teeth will be randomly assigned to two groups with the test group conducting ridge preservation and the control group healing naturally. Periodontal examination, cone beam-computed tomography (CBCT) data, and stereolithographic (STL) files obtained by intraoral scanning will be collected through the follow-up period, and bone biopsy samples would be obtained during implant surgery. The primary outcomes are the vertical and horizontal change of alveolar ridge measured on CBCT images, soft tissue contour changes evaluated by superimposing the digital impressions, alterations of mucosa thickness (as measured by superimposing the CBCT data and STL files), histological features of implant sites and periodontal parameter changes. The secondary outcomes are patient-reported post-operative reaction and conditions of simultaneous bone graft or sinus lifting procedures during implantation.

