### Participants

If a patient has unsalvageable molars as a consequence of severe periodontal disease and considers implant-retained prostheses for the extraction sockets, the patient will be suggested and reclused in this study.

The included patient should meet the following criteria:Age more than 25 yearsGood compliance and good oral hygieneDiagnosed with stage III/IV periodontitis [30]Presence of at least one hopeless molar with severe bone loss requiring extractionAt least two socket walls beyond the apex or ≥ 3 mm of the extraction socketAt least one adjacent tooth at the proximal region.

The exclusion criteria are as followed:Pregnancy or lactationPatients taking medications or having disease that would complicate bone healingPatients with surgical contraindications, such as uncontrolled hypertension or diabetes mellitusPatients with history of head and neck radiotherapySmoking more than 10 cigarettes per dayAbsence of both adjacent teethTeeth with ongoing acute pathologyTeeth extracted due to caries, endodontic failures or fractured teeth.

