### Randomizing

A series of random numbers will be generated using Excel 2021 (Microsoft Corp., Redmond, WA, USA), written on letter paper and sealed in sequentially numbered, sealed, opaque envelopes. All the patients will be assigned to two groups by simple randomization with the rate of 1:1: the test group with alveolar ridge preservation, and the control group with natural healing. All the surgical procedures will be performed by an experienced clinician, and the other clinician will conduct the clinical examination for the patients. Another two members will take charge of intraoral scanning, assessing the radiological examinations and completing statistical analysis.

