### Sample size calculation

The sample size was calculated using the Power Analysis and Sample Size (PASS) (version 15.0, NCSS, LLC, East Kaysville, Utah, USA) based on a two-sided alpha of 0.05 and power of 0.8. According to previous literature [13], the ridge width changes in one site (at 1 mm apically from the top of the alveolar crest in central buccal) of ridge preservation group and natural healing group were 1.46 mm and -0.70 mm, respectively. And the SD were 3.54 mm and 2.28 mm. After the calculation, the minimal sample size was 30 extraction sites for each group. Considering 15% non-response rate, 35 extraction sites will be included in this study for each group. Totally, 70 extraction sites will be needed.

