### Statistical analysis

Statistical analysis will be performed using the SPSS 26.0 software package (SPSS Inc., Chicago, IL, USA). Descriptive data will be reported as mean ± standard deviations. A Shapiro–Wilk test will be applied to test for normal distribution of the sample for each variable. The paired t-test or Wilcoxon signed rank sum test when the data are not normally distributed will be applied to detect changes of soft and hard tissue before and 6 months after surgery. Independent samples t tests will be performed to compare parameter means between control and test groups. A non-parametric Mann–Whitney U test will be used if parameters are not normally distributed. Baseline characteristics of the patients who are lost to follow-up and completed this study will be compared. For the missing outcome data, K-means clustering method will be used for imputation. The level of significance was set at α = 0.05.

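### The abstract randomises teeth and the Methods randomise patients; if patients are the unit and some contribute several molars, the planned site-level tests are anti-conservative and the stated power is not reached

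*Protocol article*

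**What the plan says.** Five statements in the protocol article bear on this point.

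- **Unit of randomisation, abstract (Methods):** "Teeth will be randomly assigned to two groups".
- **Unit of randomisation, Randomizing section:** "All the patients will be assigned to two groups by simple randomization with the rate of 1:1".
- **Sites per patient, Participants section:** a patient must have "at least one hopeless molar with severe bone loss". The opening sentence of that section is in the plural: "If a patient has unsalvageable molars as a consequence of severe periodontal disease and considers implant-retained prostheses for the extraction sockets". No upper limit and no index-tooth rule are given.
- **Sample size calculation:** the calculation is "based on a two-sided alpha of 0.05 and power of 0.8", and its result is that "the minimal sample size was 30 extraction sites for each group". This becomes 35 per group and 70 in total after a 15% non-response allowance. No number of patients and no design effect appear.
- **Statistical analysis:** "Independent samples t tests will be performed to compare parameter means between control and test groups", with Mann-Whitney U as the alternative when data are not normal.

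**The concern.** Randomising teeth and randomising patients are different designs. If patients are randomised, all sites of one patient fall in the same arm and form a cluster. If teeth are randomised, one patient can have sites in both arms. Current text supports each reading.

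Under patient randomisation with several sites per patient, sites within a mouth are likely to be positively correlated. A test that treats them as independent then uses too small a standard error. The p-values for the main between-group comparisons would be too small, and a sample size counted in sites would overstate the information in the trial. Under tooth randomisation the difficulty lies elsewhere: a patient treated in both ways reports pain and other reactions that may not be separable by treatment.

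**Working it through.** **1. Reproduce the stated sample size.** Inputs from the Sample size calculation section: means 1.46 and -0.70 mm, SDs 3.54 and 2.28 mm, two-sided alpha 0.05, power 0.80.

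- Difference: 1.46 - (-0.70) = 2.16 mm.
- Root mean square SD: sqrt((3.54² + 2.28²)/2) = sqrt(8.865) = 2.977 mm.
- n per group = 2 × (1.960 + 0.842)² × 8.865 / 2.16² = 29.8, so 30.
- Power at 30 by the normal approximation is 0.802. With the Welch t distribution it is 0.787, and 31 per group would be needed.

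The stated 30 is therefore reproduced, but only with every site counted as an independent observation (design effect 1).

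**2. Patients randomised, all of a patient's sites in one arm.** Let m be the mean number of sites per patient and ICC the within-patient correlation. Both are assumptions.

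- Design effect: D = 1 + (m - 1) × ICC.
- Type I error of the site-level test: 2 × (1 - Φ(1.96/√D)).
- Power of a valid analysis at 30 sites per arm: Φ(2.16/√(17.73 × D/30) - 1.96), where 17.73 = 3.54² + 2.28². The t-based value is given beside it.
- Sites per arm needed before dropout: 30 × D, rounded up.

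| m | ICC | D | Type I error | Power, normal | Power, t | Sites per arm |
|---|---|---|---|---|---|---|
| 1 | any | 1 | 0.050 | 0.80 | 0.79 | 30 |
| 1.25 | 0.1 | 1.025 | 0.053 | 0.79 | 0.78 | 31 |
| 1.25 | 0.5 | 1.125 | 0.065 | 0.75 | 0.74 | 34 |
| 1.5 | 0.1 | 1.05 | 0.056 | 0.78 | 0.77 | 32 |
| 1.5 | 0.3 | 1.15 | 0.068 | 0.75 | 0.73 | 35 |
| 1.5 | 0.5 | 1.25 | 0.080 | 0.71 | 0.69 | 38 |
| 2 | 0.1 | 1.1 | 0.062 | 0.76 | 0.75 | 33 |
| 2 | 0.3 | 1.3 | 0.086 | 0.69 | 0.68 | 39 |
| 2 | 0.5 | 1.5 | 0.110 | 0.63 | 0.61 | 45 |

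Worked line for m = 2, ICC 0.5: D = 1 + 1 × 0.5 = 1.5. Then 1.96/√1.5 = 1.600, which gives a type I error of 0.110. For power, 2.16/√(17.73 × 1.5/30) = 2.294; 2.294 - 1.96 = 0.334, and Φ(0.334) = 0.63. With 15% dropout the 45 becomes 45/0.85 = 52.9, so 53.

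A simulation of the site-level Welch test (30 sites per arm, the protocol's SDs, 40,000 runs per setting) agrees. At m = 2 the type I error is 6.2%, 8.5% and 11.2% for ICC 0.1, 0.3 and 0.5. At a mean of 1.25 sites (6 patients per arm with two sites, 18 with one) and ICC 0.1 it is 5.4%. When some patients have one site and others two, putting the mean m into the formula slightly understates the inflation.

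**3. Teeth individually randomised.** With 60 sites split 30/30 at random, two sites of one patient share an arm with probability 29/59 and are in opposite arms with probability 30/59. Same-arm pairs add covariance to the variance of the difference and opposite-arm pairs subtract it. The expected net weight is (29 - 30)/59 = -1/59, practically zero. Simulation with two sites per patient, a common SD of 2.977 mm, ICC 0.1 to 0.5 and 6,000 runs per setting gives a type I error of 4.5-5.1% and power of 79-80% at 2.16 mm. The independent-samples test therefore has no material error under this reading.

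**The case against.** The strongest objection is that the protocol permits several sites per patient but does not say that they will be enrolled. The minimum of one hopeless molar is an eligibility floor. The Intervention section and the baseline examination text speak of a single tooth, which fits one treated site per patient. With one site per patient, 30, 35 and 70 stand and the tests are valid. This objection holds as far as it goes: multi-site enrolment is not established. The plural in the Participants section points the other way, however, and no rule settles the matter.

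A reader might infer that p-values and power are wrong whenever patients contribute several sites. The documents do not support that. The error needs patient randomisation as well, and under the abstract's tooth randomisation the same test behaves properly. Nor is the test shown to be strongly conservative under tooth randomisation. That would require every patient to have exactly one site in each arm (type I error about 0.006 at ICC 0.5), whereas the protocol describes a parallel-group trial with simple randomisation.

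A reader might also suppose that patients with stage III/IV periodontitis usually have several hopeless molars. The protocol gives no such figure, and the point does not rely on it. It would likewise be too strong to say that no reported reaction could be attributed under tooth randomisation. Swelling and erythema can be recorded at a site; pain is the harder case. These are also secondary outcomes.

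Finally, a full protocol or analysis plan might contain a clustered model or an index-tooth rule. That is possible, and the absence of a model is not the point. The conflict over the unit, the sample size counted in sites and the named independent-samples tests are all stated in the article itself.

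**Conclusion.** The point holds conditionally. The contradiction over the randomised unit is certain from the text. The statistical harm follows only if the Randomizing section governs and some patients contribute more than one site. Over the values shown, the harm ranges from nothing (one site per patient), through about 5.3% type I error and 79% power (1.25 sites, ICC 0.1), to about 11% and 61-63% (2 sites, ICC 0.5). Sites per patient and ICC are assumptions throughout. If teeth are individually randomised, size and stated power are kept, and what remains is the difficulty of attributing patient-level reactions such as pain. Because the consequence differs by unit, the two statements must be reconciled before an analysis is settled. Severity: should fix.

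**What to change.** State one randomisation unit, the patient as in the Randomizing section, and correct the abstract. State whether more than one site per patient may be enrolled. Then take one of two routes.

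1. Analyse one index molar per patient, chosen by a fixed rule before the envelope is opened, and state the sample size as 30 (35 with dropout) patients per group. The t and Mann-Whitney tests then stand as regards independence.
2. Keep all sites, replace the t/Mann-Whitney comparison with a linear mixed model with a patient random intercept (or cluster-robust standard errors), and restate the power after a design effect with the assumed sites per patient and ICC shown.

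The first route costs the extra molars, which no longer count towards the target. The second costs slightly more analysis work and possibly a less favourable stated power or a larger number of sites. Neither adds visits or procedures for a given patient.

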**Fig. 3 Fig3:**
[figure not shown]
Flowchart of data collection during follow-up period

At baseline (before tooth extraction), the following data will be collected:Full-mouth peri-apical films,CBCT images (CBCT 1): CBCT images will be taken by CBCT machines (NewTom VG; Aperio Services, Italy) at a resolution of 0.125 mm with field of view size 10 × 10 cm (exposure time: 3.6 s, 110 kV, 5 mA). It will be used for assessing anatomical conditions, including the degree of bone loss and the position of maxillary sinus/mandibular canal.Stereolithography (STL) files (STL 1): intraoral scans will be taken using a TRIOS intraoral scanner (3Shape TRIOS Color, TRC, 3Shape, Denmark) to obtain a digital impression of the target area and generate an STL file, which include the selected tooth and relevant quadrant. Soft tissues contained in this digital impression will extend over the mucogingival junction.Periodontal parameters: the periodontal conditions of the ailing tooth and adjacent teeth will be assessed by measuring probing depth (PD), gingival recession (GR) and bleeding index (BI). The width of keratinized tissue (WKT) will be measured at mid-buccal aspect from the mucogingival junction to the gingival margin of the teeth. Data will be round down to the nearest 0.5 mm, and they will be collected using an UNC-15 probe (Hu-Friedy, Chicago, IL, USA).

#### 
Examination immediately after the intervention for both groups (Fig. 3)

CBCT images (CBCT 2): it will be used for superimposition and measurement. And it will be illustrated in informed consent.STL files (STL 2)

#### 
Examinations during the follow-ups before implant therapy (Fig. 3)

STL files (STL 3–6): the patients will be recalled at 2, 4, 12 weeks and 6 months after the surgery, and intraoral scans will be performed.CBCT images (CBCT 3): CBCT examination will be performed 6 months after the surgery.Post-operative reaction: the patients will be recalled at 1, 2 and 4 weeks after the surgery to report post-operative reaction, such as pain, erythema, swelling and paranesthesia.Paralleling technique films: films will be taken 6 months after the surgery.Periodontal parameters: at 6 months after the surgery, the periodontal examination indicators (PD, GR, BI and WKT) will be recorded for the adjacent teeth, and WKT of extraction area will also be measured at the buccal aspect from the central of the (expected) implant position to the buccal mucogingival junction [32].

#### 

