Examination during implant therapy (Fig. 3)

The implant therapy will be performed around 6 months after ARP/tooth extraction.Bone biopsy: during the implant placement procedure, a cylindrical bone block with a diameter of about 2 mm and length of about 5 mm will be taken out using a trephine drill (Institute Straumann AG, Basel, Switzerland). The block will be fixated in 4% formaldehyde solution at room temperature for at least one day. Then, they will receive decalcification for 3 weeks in 4.1% disodium ethylene-diamino-tetra-acetic acid-solution, the solution will be changed every 24 h. After hydration, they will be dehydrated in increasing concentrations of ethanol (from 70 to 100%), embedded in paraffin, and cut into sections with a thickness of 4 µm. Serial sagittal sections will be stained with hematoxylin–eosin. Representative regions of interest (ROIs) will be localized in the center, apically and coronally of the sample [33]. Histologic slides will be observed under light microscopes and digital images will be obtained by scanning at a magnification of × 200 for subsequent histomorphometric analysis. For the two groups, the histological composition in terms of new bone formation, residual graft particles and connective tissue will be evaluated and compared.Simultaneous bone graft & sinus lifting procedures: the conditions of bone grafting and sinus lifting during implant therapy will be recorded.

#### 
Examination during the follow-ups after implant restoration (Fig. 3)

After 6-month period of osseointegration, the superstructures will be connected to the implants. Participants will be recalled at immediately, 1-, 3-, and 6-month and then every 6 months after implant loading. During this period, the following data will be collected:STL files (STL R1, R2, and so on): intraoral scans will be performed at every appointment.Periodontal parameters: the periodontal examination indicators (PD, GR, BI and WKT) will be recorded for the implant and adjacent teeth at every appointment.Paralleling technique films: the films will be collected immediately and every 6 months after implant loading, and they will be used to evaluate the marginal bone loss (MBL).

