#### Superimposition and measurement of CBCT images and digital impressions

CBCT images: Digital Imaging and Communications in Medicine (DICOM) data will be generated and transferred to a volumetric imaging software (Mimics 21.0, Materialise, Leuven, Belgium). Residual buccal and lingual (or palatal) plate thicknesses and height of residual socket walls can be measured and recorded with vertical/horizontal reference lines and dots on CBCT 2. After Superimposition of CBCT 2 and CBCT 3, horizontal width and vertical height changes at target sites will be calculated; details are discussed in the previous literature [13, 17].STL files: these data will be generated and imported to Geomagic Studio 2021 (3D Systems Inc., Rock Hill, SC, USA). Superimposition of STL 1 and STL files for subsequent stages (STL 2–6, STL R1, and so on) will be completed for the selected areas, using identified landmarks such as cusps of adjacent teeth. After superimposition, the impressions can be aligned and manually checked for perfect matching, and changes of the contour lines of alveolar ridge can be observed and measured.CBCT data and STL files: As described in previous literature [25], CBCT 2 and STL 3 will be superimposed in Geomagic Studio 2021 (3D Systems Inc., Rock Hill, SC, USA) using three or more landmarks of adjacent teeth and so will CBCT 3 and STL 6. The vertical thickness of the crestal mucosa and horizontal thickness of the buccal and palatal/lingual mucosa and their alterations will be measured.

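### Five co-equal primary outcome families are tested parameter by parameter at 0.05, while the sample size covers one CBCT width only

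*Protocol article*

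**What the plan says.** The Abstract (Methods) opens its list with "The primary outcomes are the vertical and horizontal change of alveolar ridge measured on CBCT images, soft tissue contour changes". It continues with "alterations of mucosa thickness (as measured by superimposing the CBCT data and STL files" and ends with "histological features of implant sites and periodontal parameter changes". No outcome on the list is given the lead.

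The Methods text shows what these families contain:

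- **Mucosa thickness** (Superimposition and measurement of CBCT images and digital impressions): "The vertical thickness of the crestal mucosa and horizontal thickness of the buccal and palatal/lingual mucosa and their alterations will be measured".
- **Histology** (Examination during implant therapy): for the two groups, "the histological composition in terms of new bone formation, residual graft particles and connective tissue will be evaluated and compared".
- **Periodontal parameters** (follow-ups before implant therapy): "the periodontal examination indicators (PD, GR, BI and WKT) will be recorded for the adjacent teeth".

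The Sample size calculation uses a single variable, "the ridge width changes in one site (at 1 mm apically from the top of the alveolar crest in central buccal"), at two-sided alpha 0.05 and power 0.8. The Statistical analysis section compares parameter means between groups by independent-samples t test, or by Mann–Whitney U test if not normal. "The level of significance was set at" 0.05.

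Under Intervention, the bone substitute (DBBM) is placed only in the test group. Under Randomizing, the control group heals naturally.

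**The concern.** A trial with one alpha and one sized variable can give one confirmatory answer. Here five families share the primary label and no rule says which decides. Power is known for one CBCT width and for nothing else on the list. Testing every primary parameter at 0.05 pushes the chance of some false-positive primary above 5%, by an amount that depends on how many are counted and how closely they correlate.

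The families can also disagree. The Background and Discussion cite a review in which DBBM gave less new bone than natural healing, while ridge preservation is expected to hold ridge dimensions. New bone and ridge dimension are both primary, so a split result would leave the trial's answer to be chosen after the data are seen, in a trial that the Blinding section describes as unblinded.

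One histology component raises a separate problem. Residual graft particles are compared between a group that receives graft and a group that does not. A difference there follows from the allocation and is not evidence of efficacy.

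**Working it through.** **1. The plan's own figure.** Inputs from the Sample size calculation: mean changes 1.46 and −0.70 mm, SDs 3.54 and 2.28 mm, two-sided alpha 0.05, power 0.80.

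- Difference: 1.46 + 0.70 = 2.16 mm.
- Mean variance: (3.54² + 2.28²)/2 = (12.53 + 5.20)/2 = 8.865, so SD = 2.977 mm.
- n per group = 2 × (1.960 + 0.842)² × 8.865 / 2.16² = 29.8, rounded up to 30.

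This matches the stated 30. Power at 30 per group is 80.2% by the normal approximation and 78.7% by a Welch t calculation. The number is sound for the variable it was computed on.

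**2. Counting the primary variables.**

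| Family | Variables | Count |
|---|---|---|
| CBCT ridge change | vertical, horizontal | 2 |
| Soft tissue contour | contour change | 1 |
| Mucosa thickness | crestal, buccal, palatal/lingual | 3 |
| Histology | new bone, residual graft, connective tissue | 3 |
| Periodontal | PD, GR, BI, WKT | 4 |
| **Total** | | **13** |

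This expands the five named families using the Methods text. It is a minimum, because it counts one site, one tooth and one visit per variable.

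**3. Chance of at least one false-positive primary.** This assumes that each test is at 0.05, all null hypotheses are true, and any one significant result counts. For k independent tests it is 1 − 0.95^k:

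- k = 5 (one test per family): 1 − 0.95⁵ = 22.6%.
- k = 12 (the 13 without residual graft, whose null cannot be true): 1 − 0.95¹² = 46.0%.

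The documents give no correlations. Assuming a common correlation ρ, a simulation of 400,000 draws of correlated normal statistics with a two-sided cut-off of 1.96 gave:

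| ρ (assumed) | 5 tests | 12 tests |
|---|---|---|
| 0.3 | 21.0% | 39.6% |
| 0.5 | 18.3% | 32.0% |
| 0.7 | 14.9% | 23.3% |
| 0.9 | 10.2% | 13.5% |

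Every value exceeds 5%.

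**4. Residual graft.** Controls are zero by design. The documents give no mean or SD for the grafted group, so these are assumptions, with 30 per group and a noncentral t calculation:

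| Assumed mean | Assumed SD | Power |
|---|---|---|
| 5% | 10% | 75% |
| 10% | 15% | 94% |
| 10% or more | 10% | over 99.9% |

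By Mann–Whitney with all 30 controls at zero, p is about 0.006 if only 7 of 30 grafted biopsies contain any particle.

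**The case against.** The strongest reply has four parts.

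- **The count of 13 is an expansion.** The Abstract names five families and does not label each measurement as a separate primary. This stands. For that reason the five-test figure is shown beside the 12-test figures.
- **Independence is the extreme case.** Several variables come from the same socket, so correlation is likely. This also stands, and the result is a range. Even the lowest value, about 10% for five tests at ρ = 0.9, is twice the nominal level.
- **An adjustment or testing order may sit in a fuller protocol or analysis plan.** That is possible, and its absence from an article is not the complaint. What the article does state is five primaries of equal rank, a size based on one variable, and a single alpha. A hierarchy led by the sized variable would cost that variable no power, but the article does not say which variable leads.
- **Residual graft is one component of histology.** The protocol nowhere claims that more of it is good, and the third aim in the Background words histology in terms of ARP sites. True, but the section on implant therapy still sets it up as a comparison of the two groups within a primary family.

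A reader might infer that a positive primary result is nearly guaranteed, because residual graft differs by construction. The documents do not support this. It needs a rule that any one significant variable makes the trial positive, which is stated nowhere, and residual-graft values that are not given. Multiplicity alone does not make a positive result near certain.

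**Conclusion.** The point holds in a limited form. Five families are primary with equal rank, the size and the 80% power belong to one CBCT width site, and each parameter is tested at 0.05. If any one significant primary were taken as success, the false-positive chance would be about 23% for five independent tests. For 12 variables it would lie between about 14% and 46%, depending on an assumed correlation between 0.9 and 0. These are conditional figures, because the article fixes no success rule.

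The residual graft comparison is uninformative about benefit and likely to be significant by construction: power about 75% to over 99.9% under the assumed means and SDs. It should not count as primary evidence. None of this makes the planned number of sites wrong for the variable it was computed on.

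**What to change.** By a dated amendment, made and justified before any outcome data are reviewed:

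1. Name one primary outcome: change in CBCT ridge width from CBCT 2 (immediately after surgery) to CBCT 3 (6 months), 1 mm apical to the crest at central buccal, tested at two-sided 0.05. This is the variable already used for sizing, and 30 per group still gives about 80% power.
2. Move vertical ridge change, soft tissue contour, mucosa thickness, histology and periodontal parameters to secondary. Report them with confidence intervals and no confirmatory claim.
3. Report residual graft descriptively in the ARP arm only.

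No new data or sites are needed. By contrast, keeping all five families primary with a Bonferroni alpha of 0.05/5 = 0.01 would need 45 per group before losses by the same formula as above. Power at 30 per group would fall to about 56%.

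The sponsor gives up confirmatory claims on outcomes that were never powered. The change is also more than wording. Recruitment began on 1 March 2022, the trial is unblinded, and the two team members who handle scanning and radiological assessment also carry out the analysis. The registry entry therefore needs a justified update, with a statement that no outcome data had been reviewed when the change was made.
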